### Statistical analysis

The percentage of agreement between assessments of anesthesia depth during clinically identified possible “Deep Anesthesia Events” and “Arousal Events” from BIS and SedLine monitors and clinicians’ assessment will be analyzed with chi-square test. Kappa statistic and the standard error of kappa will also be calculated to account for the degree of agreement expected by chance. All statistical comparisons will be performed using GraphPad Prism version 8.4.3 for Windows, GraphPad Software, San Diego, California USA, (www.graphpad.com).

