**Methods:**

This prospective, non-blinded, non-randomized study will enroll 100 adult American Society of Anesthesiologists (ASA) class I-III patients presenting for elective procedures requiring general anesthesia. BIS and SedLine electrodes will be placed preoperatively according to manufacturer recommendations and their respective indices tracked throughout anesthesia induction, maintenance and emergence. The concordance between processed EEG indices and clinical assessments of anesthesia depth will be analyzed with chi-square and kappa statistic.

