**Discussion:**

Prior studies comparing brain function monitoring devices have applied both sensors on the forehead of study subjects simultaneously. With limited space and common sensor locations between devices, it is not possible to place both commercial sensor arrays according to the manufacturer’s recommendations, thus compromising the validity of these comparisons. This trial utilizes a custom interface allowing signals from sensors to be shared between BIS and SedLine monitors to provide an accurate comparison. Our results will also characterize the degree of agreement between processed EEG indices and clinical assessments of anesthetic depth as determined by the anesthesiologists’ interpretations of acute changes in blood pressure and heart rate as well as the administration, or change to the continuous delivery, of medications at these timepoints. Patient factors (such as burst suppression state or low power EEG conditions from aging brain), surgical conditions (such as use of electrocautery), artifacts (such as electromyography), and anesthesia medications and doses (such as end-tidal concentration of volatile anesthetic or hypnotic infusion dose) that lead to lack of agreement will be explored as well.

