### Data collection

Data collection will begin with a baseline set of BIS and PSI indices. Once recorded, general anesthesia will be induced with medications and doses chosen by the intraoperative anesthesia care team and documented in the electronic medical record (EMR). The depth of sedation during induction will be measured, at least, every minute using the Modified Observers’ Assessment of Alertness/Sedation (MOAAS) scale until the patient loses the eyelash reflex and achieves a score of 0. Two MOAAS scores can share the same timepoint if the patient achieves a new score less than 1 min from the prior score. The following descriptions of MOAAS scores will be used: 0 does not respond to pain; 1 does not respond to mild prodding or shaking; 2 responds after mild prodding or shaking; 3 responds after calling loudly or repeatedly; 4 responds slowly to voice with normal tone; 5 responds readily to voice with normal tone. Times indicating start of anesthesia induction, endotracheal intubation, surgical incision, and the start of electrocautery will also be recorded. Electronic, time-stamped documentation of intravenous medication doses in the EMR by the anesthesia provider will allow for retrospective review of their effects on raw and processed EEG data by investigators. Similarly, end-tidal concentrations of volatile gases will be automatically recorded in real-time within the patient’s EMR throughout the entire surgery.

Throughout the course of the surgical procedure, timepoints with acute changes of ±20% in blood pressure or heart rate from baseline values will be recorded. At these timepoints, an investigator will question the anesthesia provider regarding the suspected cause for each acute change as “Light Anesthesia”; “Deep Anesthesia”; “Volume Status”; or “Other.” The anesthesia provider will not be limited in responses for “Other.”

At the end of the surgical procedure, timepoints indicating incision closure, emergence from anesthesia, tracheal extubation, and return of consciousness will be recorded. During emergence, MOAAS will be measured every minute until the patient achieves a score greater than or equal to 4. Sensors will be removed prior to patient transport to the post-anesthesia care unit (PACU). A timeline of events and experimental recordings are shown in Fig. 4.

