### Primary outcomes

This protocol’s primary endpoint is to establish the concordance, or extent of agreement, between the processed EEG indices from BIS and SedLine monitors and the real-time clinical assessments of anesthetic depth by clinicians during “Deep Anesthesia Events” and “Arousal Events.” Investigators will retrospectively review the EMR to identify interventions made by the anesthesia providers during 10 min surrounding (5 min before and after) periods of burst suppression noted on raw EEG or acute changes in blood pressure or heart rate ± 20% from baseline values. The performace of processed EEG indices surrounding periods of burst suppression on raw EEG will also be analyzed.

Clinically identified possible “Deep Anesthesia Events” are defined as acute decreases in blood pressure or heart rate greater than or equal to 20% from the patient’s preoperative baseline values. The clinical diagnosis of “Deep Anesthesia” coupled with any of the following on the raw EEG, BIS or SedLine monitors indicates agreement: burst suppression on raw EEG, processed EEG index value consistent with a deep anesthesia state per manufacturer recommendations (below 40 for BIS or below 30 for SedLine), or an acute decrease in the processed EEG index by 10 over the same index 5 min prior to the event. The actions of the anesthesia providers will also be examined during these timepoints, in particular the administration of hypnotic (such as propofol or volatile agent) or analgesic medication.

Clinically identified possible “Arousal Events” are defined as acute increases in blood pressure or heart rate greater than or equal to 20% from the patient’s preoperative baseline values. The clinical diagnosis of “Light Anesthesia” coupled with any of the following on the BIS or SedLine monitors indicates agreement: processed EEG index value that signifies inadequate anesthesia per manufacturer recommendations (greater than 60 for BIS or greater than 50 for SedLine), or an acute increase in processed EEG index by 10 over the same index 5 min prior to the event. The actions of the anesthesia providers will also be examined during these timepoints, in particular the administration of hypnotic (such as propofol or volatile agent) or analgesic medication.

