## Discussion

We present a novel data collection system that will support a prospective, non-blinded, non-randomized study to concurrently compare the performance of processed EEG indices from BIS and SedLine monitors. Although prior studies have demonstrated marginal correlation between the BIS and SedLine monitors with various anesthetic agents, these studies have been limited because they require non-standard sensor locations in order to apply both sensor arrays on the forehead of study subjects [22, 23]. Because not all sensors are positioned according to manufacturer’s instructions, the validity of prior comparisons is compromised. In addition, our inclusion of standardized clinical observations (acute changes in blood pressure or heart rate) in real-time and collection of raw and processed EEG waveforms will allow us to investigate the agreement of BIS and PSI indices across a wide range of anesthetic depth and establish correlations to clinical assessments and medication administration.

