Our data may not be representative for all patient groups, particularly pediatric patients and those with severe systemic disease (ASA IV or V). Patients undergoing surgical procedures in the prone or lateral positions are also not represented given the variable contact between the EEG sensors and the patients’ forehead skin in these positions and the inability to reliably troubleshoot these problems. Additionally, interference from electrocautery limits our ability to reliably evaluate processed EEG indices in patients undergoing procedures of the head, neck, and face.

Real-time, simultaneous comparison of brain function monitoring devices using this electronic interface is the only way by which we can confidently and accurately investigate differences in proprietary algorithms. Our study design and custom engineered setup will allow a valid comparison of the BIS and PSI indices. Further research with our design will be necessary given the potential benefits of accurately assessing anesthetic depth.

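### The stated chi-square test is not said to be paired and does not measure agreement; kappa covers agreement with the clinician, but nothing stated validly compares BIS with SedLine

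*Protocol article*

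**What the plan says.** The Statistical analysis section states that the percentage of agreement between the monitors and the clinician's "assessment will be analyzed with chi-square test". Its next sentence adds: "Kappa statistic and the standard error of kappa will also be calculated to account for the degree of agreement expected by chance". The Methods part of the abstract says the same in short: "The concordance between processed EEG indices and clinical assessments of anesthesia depth will be analyzed with chi-square and kappa statistic". The sentence on the chi-square test does not say whether it compares the two devices' agreement percentages or cross-tabulates each device against the clinician. It names no paired version of the test.

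The Primary outcomes section sets the endpoint: "This protocol’s primary endpoint is to establish the concordance, or extent of agreement, between the processed EEG indices from BIS and SedLine monitors" on one side and the clinician's real-time assessment on the other. It gives rules by which each device either agrees or does not agree with the clinician at an event.

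Comparing the devices is also a stated aim. The Discussion presents a system to "concurrently compare the performance of processed EEG indices from BIS and SedLine monitors", and the abstract says: "This trial utilizes a custom interface allowing signals from sensors to be shared between BIS and SedLine monitors to provide an accurate comparison". Events are collected throughout surgery. According to Data collection, "timepoints with acute changes of ±20% in blood pressure or heart rate from baseline values will be recorded", with no limit of one per patient.

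**The concern.** BIS and SedLine are read at the same event, in the same patient, against one clinician rating. The two agree/disagree results at an event are therefore a matched pair. An ordinary chi-square test of two percentages assumes independent samples. An ordinary chi-square test on a device-by-clinician table asks whether the ratings are associated, which is a different question from whether they agree.

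The comparison between devices is what is at stake. If the ordinary test is used for it, a real difference in agreement may be missed. If the test is run on each device's table instead, a small p-value may be read as proof of agreement, and BIS is never tested against SedLine. Several events from one patient add a second, separate problem for any test that counts events as independent.

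**Working it through.** The article gives no agreement rate, significance level, between-device correlation or number of events per patient, and calls its sample size of up to 100 patients arbitrary. There is no figure of the plan to reproduce. The values below are assumptions chosen to show direction and rough size, with a two-sided 5% level.

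**1. Chi-square as a comparison of the two agreement percentages.** Let p1 and p2 be the devices' agreement proportions, q = 1 − p, n the number of events (one per patient here), and φ the correlation between the two binary results.

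Under equal agreement p, the true variance of the difference is 2pq(1 − φ)/n, while the unpaired test uses 2pq/n. Its true rejection rate is therefore 2[1 − Φ(1.96/√(1 − φ))]. The simulations used n = 100, p = 0.60 and 100,000 runs.

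| φ | Formula | Simulated, unpaired | Simulated, McNemar |
|---|---|---|---|
| 0.3 | 1.9% | 2.0% | 5.1% |
| 0.5 | 0.56% | 0.57% | 5.3% |
| 0.7 | 0.03% | 0.04% | 4.7% |

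Power for 0.70 v 0.60 with φ = 0.5 and n = 100:
- True SD of the difference: √[(0.21 + 0.24 − 2 × 0.5 × √(0.21 × 0.24))/100] = √(0.2255/100) = 0.0475.
- Unpaired cut-off: 1.96 × √(2 × 0.65 × 0.35/100) = 0.132. Power is about Φ[(0.10 − 0.132)/0.0475] = Φ(−0.68) = 25%; simulated 25%.
- McNemar: the probability that the devices differ at an event is 0.70 + 0.60 − 2 × 0.532 = 0.2355, so the cut-off is 1.96 × √(0.2355/100) = 0.095. Power is about Φ[(0.10 − 0.095)/0.0475] = Φ(0.10) = 54%; simulated 56%.

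Simulated power over a range, unpaired v paired: at 100 events, 28% v 42% (φ 0.3), 25% v 56% (φ 0.5) and 19% v 79% (φ 0.7). At 300 events, 77% v 87%, 81% v 96% and 87% v more than 99%. With φ = 0 the two tests are practically the same (about 31% each at 100 events).

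**2. Chi-square on a device-by-clinician table.** Take the tables [40, 10; 10, 40] and [10, 40; 40, 10]. All margins are 50, so each expected count is 25. Both tables give chi-square = 4 × 15²/25 = 36.0 (p = 2 × 10⁻⁹).
- First table: agreement 80%, kappa = (0.80 − 0.50)/(1 − 0.50) = +0.60.
- Second table: agreement 20%, kappa = (0.20 − 0.50)/(1 − 0.50) = −0.60.

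Chi-square cannot tell these apart. Kappa can.

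**3. Two kappas as a device comparison.** The variance of the difference is Var(κ_BIS) + Var(κ_SedLine) − 2 Cov(κ_BIS, κ_SedLine). The planned standard errors supply the first two terms. The covariance is not zero, because both kappas use the same events and the same clinician ratings, and no stated quantity estimates it.

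**4. Several events per patient.** The simulation used 100 patients, equal true agreement and 4,000 runs. The assumptions were a shared patient effect with SD 1 on the logit scale and, for the middle two columns, a further patient effect specific to each device, also with SD 1.

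| Events per patient | Unpaired, with device-specific effect | McNemar, with device-specific effect | McNemar, without it |
|---|---|---|---|
| 1 | 3.9% | 4.9% | 4.8% |
| 3 | 6.5% | 8.4% | 4.9% |
| 5 | 9.9% | 12.2% | 5.1% |
| 10 | 16.8% | 20.2% | 4.7% |

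The excess appears only when the difference between devices varies from patient to patient and patients contribute more than one event. McNemar's test respects the pairing and is still affected.

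**The case against.** The strongest reply is that the plan already measures agreement. Kappa stands in the sentence after the chi-square test, and it answers the primary endpoint, which is concordance with the clinician and not a difference between devices. This stands: a reader who inferred that agreement is left to chi-square alone would be wrong.

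A reader might also infer that ignoring the pairing makes the device comparison invalid, in the sense of producing false positives. The working does not support that. With positively correlated devices the unpaired test rejects too rarely. Inflated error comes from repeated events within patients, under variances that the article does not give.

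Nor do the documents say that the interface was built so that each event serves as its own control. The reason they give is electrode placement: both commercial arrays cannot be positioned as the manufacturers recommend. That benefit survives any choice of test. The Discussion's claim, "Our study design and custom engineered setup will allow a valid comparison of the BIS and PSI indices", concerns the design and setup rather than the test.

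Finally, the words chi-square test do not strictly exclude McNemar's version, and a condensed article may leave modelling detail to a fuller document. Both points are fair, but they do not remove the concern. The article names a method twice, and the ordinary form of that method suits neither reading. McNemar's version would still leave the clustering.

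**Conclusion.** The concern holds in limited form. The chi-square test as written either treats matched results as independent, which costs power, or tests association, which is neither agreement nor a comparison of devices. Kappa with its standard error is a suitable measure of each device's agreement with the clinician but does not compare BIS with SedLine. No stated analysis makes that comparison with the pairing and the patient as cluster respected, although it is a declared aim.

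The loss is roughly 25% against 56% power for 100 events, 0.70 v 0.60 and φ = 0.5. It grows with φ and vanishes at φ = 0. Positive φ is plausible because the two results share an event and a clinician rating, but its value is an assumption. Clustering could push error the other way, so the net direction of error for the planned test cannot be known from the article. The mirrored-table result and the covariance argument need no assumption about the trial's data.

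**What to change.** - Keep kappa for each device as the measure of agreement with the clinician, and give it a patient-clustered 95% confidence interval.
- Do not use chi-square as evidence of agreement.
- Compare the devices by the within-event paired difference in agreement, BIS minus SedLine, and by the difference in kappa. Give each a 95% confidence interval from a bootstrap that resamples whole patients. For the difference in agreement, a GEE with device as a within-event factor and patient as cluster would also serve.
- Do not substitute event-level McNemar unless each patient contributes a single event.

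The cost is a change of analysis wording and somewhat more analysis work, probably outside the named software. No new data are needed. The article reports that recruitment is under way, so the change could still be specified before the final analysis.

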### Study population

Written informed consent will be obtained from all study participants or their surrogates. We plan to enroll up to 100 patients in this study to observe whether or not the custom built passive interface hardware allows for accurate, simultaneous comparison of BIS and SedLine devices. Because of the absence of any comparative data, this sample size was arbitrarily chosen so that the study participants will include a heterogenous group of surgeries, comorbid conditions, and patient demographics. All patients will meet the following criteria:

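### The chi-square test and the usual standard error of kappa treat a patient's repeated events as independent, so the precision of the primary concordance is overstated where events correlate within patients

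*Protocol article*

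**What the plan says.** Under Data collection, "timepoints with acute changes of ±20% in blood pressure or heart rate from baseline values will be recorded", and at these timepoints "an investigator will question the anesthesia provider regarding the suspected cause for each acute change". No maximum per patient and no first-event rule is given.

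Under Primary outcomes, these falls and rises, each measured against the patient's own preoperative baseline, are the possible Deep Anesthesia and Arousal Events. The primary endpoint is the concordance of the BIS and SedLine indices with the clinician's assessment during them.

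Under Statistical analysis, percentage agreement goes to a chi-square test, and "Kappa statistic and the standard error of kappa will also be calculated to account for the degree of agreement expected by chance". On software: "All statistical comparisons will be performed using GraphPad Prism version 8.4.3 for Windows". No patient-level summary, clustered variance, bootstrap, GEE or mixed model is named.

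Under Study population, "We plan to enroll up to 100 patients in this study", and "this sample size was arbitrarily chosen so that the study participants will include a heterogenous group of surgeries". The limitations in the Discussion do not mention repeated events.

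**The concern.** The unit of analysis is the event, but the unit sampled is the patient. All events from one patient share one preoperative baseline, one set of electrodes placed before surgery, and one brain. The abstract itself lists patient factors, such as low-power EEG in the aging brain, among the causes of disagreement to be explored. Agreement is therefore likely to be more alike within a patient than between patients.

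The Pearson chi-square and the usual standard error of kappa count each event as a fresh, independent observation. With positive within-patient correlation, the number of events overstates the information. The sample size rests on no precision calculation, so the reported standard error is the reader's only guide to how well the primary endpoint has been estimated.

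**Working it through.** **Figure to reproduce.** None. The article states no alpha, power, kappa target, precision or expected number of events. What follows is an illustration.

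**Inputs.** 100 patients (Study population). Assumed: m = 5 or 10 events per patient, and a range of within-patient correlations.

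**1. Percentage agreement as a single proportion.** The design effect is DE = 1 + (m − 1) × ICC. The true standard error is √DE times the independence one, and a nominal 95% interval covers 2Φ(1.96/√DE) − 1.

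- m = 5, ICC 0.2: DE = 1 + 4 × 0.2 = 1.8; √1.8 = 1.34; 1.96/1.34 = 1.46; coverage about 86%. The 500 events carry the information of 500/1.8 = 278.
- m = 10, ICC 0.2: DE = 1 + 9 × 0.2 = 2.8; √2.8 = 1.67; 1.96/1.67 = 1.17; coverage about 76%.
- A beta-binomial simulation with mean agreement 0.70 gave 85.3% and 76.1%.

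**2. Kappa and the clinician-versus-index chi-square.** The design effect above does not carry over to these statistics, so they were simulated. Clinician and index ratings were dichotomised latent normal variables, with a patient effect of the stated latent correlation in each rating. Each setting had 3,000 runs. Kappa was about 0.33 in the kappa runs. In the chi-square runs clinician and index were unassociated.

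| Events per patient | Latent correlation | True SD of kappa / usual SE | Coverage of kappa ± 1.96 SE | Chi-square type I error |
|---|---|---|---|---|
| 5 | 0.2 | 1.04 | 93.6% | 5.5% |
| 5 | 0.4 | 1.11 | 91.8% | 8.5% |
| 5 | 0.6 | 1.24 | 88.4% | 13.2% |
| 10 | 0.2 | 1.05 | 93.7% | 7.0% |
| 10 | 0.4 | 1.26 | 88.4% | 11.9% |
| 10 | 0.6 | 1.51 | 80.4% | 21.5% |

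With one event per patient, or zero correlation, the ratio was about 1.0 and the type I error 4-6%. Clustering is therefore what drives the table.

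**3. Cross-check of the chi-square column.** With no association, the variance is inflated by about 1 + (m − 1)·r², where r = (2/π)·arcsin(latent correlation) is the within-patient correlation of each dichotomised rating. At latent correlation 0.6, r = 0.41 and r² = 0.168.

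- m = 5: 1 + 4 × 0.168 = 1.67; √1.67 = 1.29; 1.96/1.29 = 1.52; error about 13%.
- m = 10: 1 + 9 × 0.168 = 2.51; √2.51 = 1.58; 1.96/1.58 = 1.24; error about 21.6%.

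Both match the simulation. The inflation depends on the product of two correlations, which is why it is mild when both are low.

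**4. BIS versus SedLine.** Both devices are scored on the same events. A chi-square that treats the two agreement rates as independent samples ignores this pairing. In the same simulation its type I error was about 1% without clustering and about 1-6% with it. The two faults pull in opposite directions.

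**The case against.** The strongest reply has three parts.

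- **Estimation, not decision.** The primary aim is to estimate the extent of agreement. No success threshold, alpha or kappa target depends on the standard error or p-value, and the point estimates remain valid. This stands, with the note that estimates pooled over events give more weight to patients with many events. It limits the damage but does not make the reported precision right.
- **Unknown size.** Events per patient and within-patient correlation are not given, and at low correlation the effect on kappa is only 4-5%. This also stands. The direction for kappa and for clinician-index association is clear whenever positively correlated events recur; the size is not.
- **An article condenses its protocol.** Detail may sit elsewhere, but the article does not leave the method open. It names the test, the standard error and one package for all comparisons.

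Some stronger readings are tempting but unsupported:

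- A reader might say the planned confidence intervals are wrong. The section names a test and a standard error, and no intervals.
- A reader might take error rates from the single-proportion design effect as those of the planned chi-square. They are higher than the simulated rates for clinician against index.
- A reader might infer that false-positive device differences are inflated. Pairing prevents that conclusion.
- A reader might see double counting in the 10-minute window, "during 10 min surrounding (5 min before and after) periods of burst suppression noted on raw EEG or acute changes". That window serves record review of interventions. Agreement is scored on the index value, or on its change of 10 from 5 minutes earlier, so the window does not show that events 5 to 10 minutes apart share scoring data.
- A reader might assume one anesthesia provider per patient. The text speaks of providers and a care team.

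**Conclusion.** The point holds. Followed as written, the plan gives a standard error of kappa that is too small, and p-values for clinician-index association that are too small, whenever patients contribute several positively correlated events. Any interval built from that standard error would be too narrow.

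Assuming 100 patients with 5 to 10 events each, the range runs from slight (true spread of kappa 4-5% above the usual standard error, type I error 5.5-7%, at latent correlation 0.2) to material (24-51% above, type I error 13-21.5%, at 0.6). An independence interval for percentage agreement, taken as a single proportion, would cover about 86% or 76% at ICC 0.2. Neither event counts nor correlations come from the documents. For BIS against SedLine, the test is unsuitable if applied unpaired, but the direction of its error is not fixed.

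**What to change.** In Statistical analysis:

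1. Report percentage agreement and kappa, for each device and event type, with standard errors and 95% confidence intervals from a bootstrap that resamples whole patients. GEE or another cluster-robust variance with patient as the cluster would also serve.
2. Compare BIS with SedLine by a paired analysis clustered on patient, for example the same bootstrap applied to the difference in agreement or in kappa.
3. Replace the single-package sentence with wording that allows software able to do this.
4. Optionally, add a sensitivity analysis on the first event of each type per patient.

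Nearby events should not be merged for this purpose. That would discard ratings the protocol collects for each acute change, and clustered inference already answers the defect.

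The cost is revised wording, a short script and somewhat wider intervals. No new data are needed, and Trial status says the study is still recruiting, so the change can be made before the final analysis.
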